### 5.4.2. Withdrawal Procedures

In the event that the decision is made to permanently discontinue the study drug, the subject will be withdrawn from the study and the EOT visit should be conducted. Reasonable efforts should be made to have the subject return for a follow-up visit. The last date of the last dose of study drug and the reason for subject withdrawal will be recorded in the eCRF.

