| \| **Primary Objective** \| **Primary Endpoint** \| \| --- \| --- \| \| Compare the efficacy of ruxolitinib in combination with corticosteroids versus corticosteroids in terms of overall response rate (ORR) at Day 28 in subjects with acute graft-versus-host disease (acute GVHD). \| ORR at Day28, defined as the proportion of participants demonstrating a complete response (CR), or partial response (PR) \| \| **Secondary Objective** \| **Secondary Endpoints** \| \| Compare additional response and longer-term efficacy outcomes between treatment cohorts. \| Durable ORR at Day56, defined as the proportion of patients in each arm whose response on day 28 lasts until day 56 after randomization. \| \| DOR at Month 6 for responders will be calculated. The DOR is defined from the time of the onset of response to loss of response. Subjects who died or discontinued will be censored at the  death date or the previous assessment. \| \| Response duration, defined as the time from the first response to the first recurrence/progression of acute GVHD or additional immunosuppressants for GVHD. \| \| NRM at Month 24, defined as the time from enrollment to death due to any causes other than hematologic disease relapse. \| \| Cumulative incidence of relapse (CIR) at Month 24, defined as the proportion of subjects whose underlying hematologic disease relapses. \| \| Disease-free survival (DFS) at Month 24, defined as the time from enrollment to relapse of primary disease or death from any causes, whichever occurred first. \| \| Failure-free survival (FFS) at Month 24, defined as the time from randomization to disease relapse or progression, non-relapse mortality, or the addition of new therapy for acute GVHD. \| \| Overall survival (OS) at Month 24, defined as the time from randomization to death due to any causes. \| \| Assess the incidence and severity of adverse events (AEs) and serious adverse events. \| Clinical safety data (eg, AEs, infections) will be tabulated and listed. \| \| Evaluate the use and discontinuation of  corticosteroids. \| Average and cumulative corticosteroid dose at Days 365; \| \| Evaluate the use and discontinuation of  immunosuppressive medications. \| Proportion of subjects who discontinue immunosuppressive medications at Days365. \| \| Evaluate the incidence of recurrent acute GVHD \| Incidence rate of recurrent acute GVHD through Month 24. \| \| Evaluate the incidence of cGVHD. \| Incidence rate of cGVHD at Month 24. \| \| **Overall Study Design:**  This trial is an open-label, multicenter, prospective randomized two-arm phase II study comparing the efficacy and safety of ruxolitinib plus methylprednisolone (1 mg/kg) vs. methylprednisolone (2 mg/kg) alone. The biomarkers of acute GVHD, such as sST2, sTNFR1, IL-6, IL-8, and REG3α will be tested at acute GVHD onset. Patients with newly diagnosed intermediate-risk or high-risk acute GVHD, as defined by Minnesota acute GVHD risk score and the biomarker score will be included. The treatment efficacy will be evaluated with respect to the level of biomarkers and clinical manifestations. Written informed consent must be obtained from the patients before enrollment in the study. The consent form and related materials are available from the corresponding author on request.  **Study Population:**  Eligible patients with intermediate-risk or high-risk acute GVHD graded according to the modified Glucksberg criteria, Minnesota acute GVHD risk score and the biomarker score and untreated with systemic acute GVHD therapy will be enrolled in this study.  **Key Inclusion Criteria:**   - Male or female, 14 to 65 years old. - Have undergone first allogeneic hematopoietic stem cell transplantation (allo-HSCT) from any donor source using bone marrow, peripheral blood stem cells, or cord blood for hematologic malignancies. - Develop a de novo acute GVHD, defined as intermediate- or high-risk using the Minnesota acute GVHD risk score and MAGIC biomarker algorithm.   **Key Exclusion Criteria:**   - Has received more than one allogeneic stem cell transplant. - Female patients with pregnant or breast-feeding. - Has Acquired Immune Deficiency Syndrome (AIDS), or hepatitis B/C infection, uncontrolled bacterial, fungal, or viral infections. - Allergies to ruxolitinib. - Vital organ dysfunction unrelated to GVHD, including persistent bilirubin abnormalities or severe heart and respiratory diseases. - Relapse of the primary disease or graft rejection after transplantation. - Presence of GVHD overlap syndrome. - Presence of cGVHD or associated clinical signs or DLI-induced acute GVHD or interferon. - Previous history of JAK1/2 inhibitor treatment after transplantation, except JAK inhibitors administered before the transplantation. - absolute neutrophil count (ANC) <0.5×10^9^/L or platelet count (PLT) < 20×10^9^/L - Serum creatinine > 2.0 mg/dL or creatinine clearance < 40 mL/min measured or calculated by Cockroft-Gault equation. - Patients with poor compliance should not be included in the study based on the judgment of the research team, for example if they refused to take medicine at will many times during the previous treatment.   **Study Drug, Dosage, and Mode of Administration:**  **Ruxolitinib plus corticosteroids treatment (ruxolitinib group):**  The initial dose of methylprednisolone is 1 mg/kg/day intravenously given in this arm for at least 7 days. The dosage of ruxolitinib is 5 mg PO QD. CSA will be administered intravenously at a dose of 2 mg/kg twice daily, targeting minimum concentration levels of 150–250 ng/mL. If GVHD response to treatment is assessed as PR/CR at 7 days, methylprednisolone will be tapered, followed by reduction and discontinuation of CSA and then ruxolitinib. The reduction of the methylprednisolone in the ruxolitinib group is gradual, suggesting it be tapered off over 6 weeks as follows: dosage reduced to 0.6 mg/kg/day, 0.4 mg/kg/day, 0.3 mg/kg/day, 0.25 mg/kg/day, and 0.18 mg/kg every 5 days, followed by 0.1 mg/kg/day at week 4, 0.1 mg/kg every other day after 5 days and stopped at week 6. After steroid discontinuation and CR or stable PR maintained for 6 weeks, CSA is tapered over 60 days. After CSA discontinuation and no presence of recurrent GVHD, ruxolitinib is tapered off over 90 days, which is totally maintained for approximately 6 months.  **Corticosteroid treatment (corticosteroids group):**  The initial dose of methylprednisolone is 2 mg/kg/day given twice daily for at least 7 days and then reduced. The dosage of methylprednisolone in the corticosteroids group is decreased gradually after CR and tapered off over 10 weeks as the following: dosage reduced to 1 mg/kg/day to 0.6 mg/kg/day, 0.4 mg/kg/day, 0.3 mg/kg/day, 0.25 mg/kg/day, and 0.18 mg/kg every 7 days, and then 0.1 mg/kg/day at week 4, 0.1 mg/kg every other day after 5 days, and stopped at week 10. CsA was administered intravenously at a dose of 2 mg/kg twice daily, targeting minimum concentration levels of 150–250 ng/mL. The recommended duration of CsA is 6 months.  In both arms, for refractory acute GVHD, i.e., the progression of GVHD after 3 days of therapy, no improvement within 7 days, or no CR after 14 days of therapy, the second-line therapy will be started. For refractory acute GVHD or recurrent acute GVHD, basiliximab may be used as second-line therapy, and other alternative drugs included methotrexate or mesenchymal stem cells may be used at the researcher’s decision. For refractory acute GVHD, methylprednisolone is discontinued and CsA is continued in both arms. Prolonged maintenance of ruxolitinib is used in the ruxolitinib group. A standardized follow-up booklet is given to each enrolled patient for recording the dose, frequency, and administration method of the drugs. **Estimated Duration of Participation:** Subject participation is expected to average 24 months, which includes the following:   - A screening period lasting up to 28 days. - A treatment period lasting as long as the subject is benefiting from treatment. - A safety follow-up period lasting 180 days after treatment ends. - A survival follow-up period lasting until death or study withdrawal. \| \| \| **Estimated Number of Subjects:** 198 subjects. \| \| \| **Principal Coordinating Investigator:** [name] \| \| \| **Statistical Methods:**  The sample size is calculated according to the primary endpoint (ORR) of the study. Based on our published phase I study of 32 acute GVHD patients who received steroids as first-line therapy, an expected proportion of 55% for the patients treated with corticosteroids only was established. Based on our published data of patients with acute GVHD grade I–IV who received steroid-ruxolitinib (5 mg/day) as first-line therapy, the ORR was 82.05%. Patients with acute GVHD grade I were also included in the phase I analysis. Thus, an expected proportion of 75% for the patients treated with steroid-ruxolitinib (5mg/day) was established. This study is planned to detect a response difference between treatment arms at a two-sided significance level α=5% with a power of 1-β=80%. The sample size was estimated using PASS software based on the primary endpoint (ORR). Allowing a withdrawal rate of 10%, 198 patients (99/group) will be required.  Continuous data are described as median with interquartile range (IQR) or mean and standard deviation (SD) according to the normality of distribution. The categorical data are described as n (%). The ORR was calculated with its 95% confidence interval (CI) and compared by the stratified Cochran–Mantel–Haenszel test. Additionally, a logistic regression model, which included aGVHD risk (high vs. intermediate), and disease status before transplantation (CR vs. no CR) as covariates, was established to explore the association between treatment and ORR on day 28. Post-hoc subgroup analysis was performed by biomarker risk, age and GVHD grade, although these were not prespecified in the protocol. The cumulative incidence of recurrent aGVHD was analysed using the Fine and Gray test in a competing risk framework. The Kaplan–Meier method was used to estimate the ORR on day 56, OS, DFS, and FFS, and the log-rank test was used to evaluate the difference between the groups. The cumulative incidence rates of NRM and relapse were estimated using a competing risk model and compared using the Fine and Gray test. A Cox proportional hazard regression model was used for multivariable regression analysis for OS and DFS. Multivariable regression analysis was performed for NRM using the Fine–Gray proportional hazard regression for competing events. The following variables were included in the univariable analysis: primary disease, cytogenetic risk, age and gender of the donor and recipient, source of graft, treatment arm, aGVHD risk, and disease status before transplantation. Variables with P<0.1 in univariate analysis or variables known to influence the outcomes were included in the multivariable analysis. Competing events were defined as follows: for GVHD, death without the event; for relapse, death without relapse; and for NRM, relapse. Any difference for which the two-sided P<0.05 was considered statistically significant. All analyses were carried out using SPSS 22.0 software (IBM Corporation, Armonk, NY, USA) or R version 4.1.2 (www.cran.r-project.org). All statistical analyses were based on the intend to treat set. \| \| | |

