## 4.6. Duration of Treatment and Subject Participation

After signing the informed consent form (ICF), screening assessments may be completed over 1-2 days. Each subject enrolled in the study may continue to receive study treatment as long as benefit is being observed and/or treatment withdrawal criteria are not met. If the subject discontinues study treatment, the treatment period will end, and the subject will enter the follow-up period. The safety follow-up period will last 365 days, and the survival follow-up period will last until death or study withdrawal. Study participation is expected to average approximately 24 months per individual subject but may vary based on clinical outcomes.

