## 4.7. Overall Study Duration

The study begins when the first subject signs the informed consent. Subjects who are still on-study at the time of the primary endpoint analysis will continue to receive study treatment until treatment withdrawal criteria are met. All subjects will be followed for survival until death, withdrawal of consent, or the end of the study, whichever occurs first. The study will end once 75% of subjects have died or are lost to follow-up. Provisions will be made to ensure access to treatment for subjects who are continuing to benefit from study treatment at the time of study completion.

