## 5.4. Withdrawal of Subjects from Study Treatment

The decision to discontinue study treatment will not constitute study completion. In the event that the decision is made to discontinue study treatment, the treatment period will be considered complete, and the follow-up period will begin.

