### 5.4.1. Withdrawal Criteria

Subjects must be withdrawn from study treatment for the following reasons:

- The subject has experienced an unacceptable toxicity.
- Relapse of underlying malignancy.
- The subject is unable to tolerate ruxolitinib at a dose of 5 mg QD.
- Additional systemic therapy is required for GVHD progression or lack of response, including corticosteroid doses greater than those used on Study Day 1.
- Further participation would be injurious to the subject's health or well-being, in the investigator's medical judgment.
- The subject becomes pregnant.
- Consent is withdrawn.
- The study is terminated by the sponsor.

A subject **may** be withdrawn from study treatment as follows:

- If, during the course of the study, a subject is found not to have met eligibility criteria, then the medical monitor, in collaboration with the investigator, will determine whether the subject should be withdrawn from the study.
- If a subject is noncompliant with study procedures or study drug administration in the investigator's opinion, the sponsor should be consulted for instruction on handling the subject.

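### Section 5.4.2 withdraws patients from the study when study drug is permanently stopped, against the rest of the protocol and the intention-to-treat Month-24 endpoints

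*Protocol*

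**What the plan says.** The sentence at issue opens Section 5.4.2: "In the event that the decision is made to permanently discontinue the study drug, the subject will be withdrawn from the study". It adds an end-of-treatment visit and asks sites to make reasonable efforts to bring the patient back for a follow-up visit.

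Other parts of the protocol give the opposite instruction:

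- Section 5.4: "The decision to discontinue study treatment will not constitute study completion", and after the decision to stop, "the treatment period will be considered complete, and the follow-up period will begin".
- Section 4.6: "If the subject discontinues study treatment, the treatment period will end, and the subject will enter the follow-up period".
- Section 4.7: "All subjects will be followed for survival until death, withdrawal of consent, or the end of the study, whichever occurs first".
- Section 5.4.2, later text: safety follow-up is required after withdrawal from treatment, and data collection ends only when the patient actively withdraws consent for it.
- Section 5.4.3: study completion means death, or stopping treatment together with withdrawn consent for follow-up data.
- Section 6.5.3: patients with GVHD progression or a new GVHD therapy are contacted at least every 8 weeks for survival and new therapy.

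On who must stop treatment, Section 5.4.1 lists among the mandatory reasons: "Additional systemic therapy is required for GVHD progression or lack of response, including corticosteroid doses greater than those used on Study Day 1". On analysis, the Synopsis says: "All statistical analyses were based on the intend to treat set". Section 8.4 includes every randomised patient in the primary analysis of all outcomes and expects under 10% missing values. Section 2 sets NRM, relapse, DFS, FFS, OS and chronic GVHD at Month 24.

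**The concern.** Leaving treatment and leaving the study are different events, and the first sentence of 5.4.2 merges them. A site that reads only that sentence has grounds to close the patient's record once study drug stops for good.

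Treatment failure is a mandatory reason to stop treatment under 5.4.1, and failure is prognostic. Patients lost at that point would enter the Kaplan–Meier and Fine–Gray analyses as if their later risk matched that of patients still followed. Relapse and new GVHD therapy are known when they trigger the stop. What is exposed is what comes afterwards: later death (OS, NRM), later relapse (CIR, DFS) and chronic GVHD. Some patients who stop before Day 28 could also lack a Day-28 response assessment. Data that were never collected cannot be recovered in the analysis.

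**Working it through.** **Inputs.** ORR 55% control and 75% ruxolitinib, two-sided α 0.05, power 80%, 10% withdrawal, 99 per arm (Sections 4.5.2 and 8.1); 1:1 allocation (Section 4.4).

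**The plan's own figure.** Pooled-variance two-proportion formula without continuity correction, mean proportion 0.65:

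n = [1.960·√(2·0.65·0.35) + 0.842·√(0.55·0.45 + 0.75·0.25)]² / 0.20² ≈ 88.1, so 89 per arm. Then 89/0.90 = 98.9, so 99 per arm and 198 in total. The stated figure is reproduced and is not in question.

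**Illustrative size of a literal reading.** The protocol gives no discontinuation rates. I take expected Day-28 non-responders as a stand-in for treatment failures who stop study drug:

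- Control: 99 × 0.45 = 44.6.
- Ruxolitinib: 99 × 0.25 = 24.8 at most.

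The ruxolitinib figure needs a range. For refractory GVHD the Synopsis stops methylprednisolone in both arms but maintains ruxolitinib in the ruxolitinib arm, and Section 5.1.1.1 allows the same. Such patients may not count as having permanently stopped study drug.

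| Assumed share of ruxolitinib failures who stop | Control | Ruxolitinib | Total | Share of 198 |
|---|---|---|---|---|
| 0% | 44.6 | 0 | 44.6 | 22.5% |
| 50% | 44.6 | 12.4 | 56.9 | 28.8% |
| 100% | 44.6 | 24.8 | 69.3 | 35.0% |

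Each total exceeds the 10% allowance.

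**Sensitivity to other stops (100% row).** If a further 5% to 30% of responders in each arm stopped for other reasons (assumed), failures would still be 92% to 64% of those lost. Intolerance of ruxolitinib is a stop reason in one arm only and could narrow the gap. With no stops among control responders, losses would be equal if (44.55 − 24.75)/(99 × 0.75) = 27% of ruxolitinib responders stopped.

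**Possible effect on a Month-24 endpoint.** Assume 24-month mortality depends only on response, and that lost failures contribute no observed deaths. With 20% mortality in responders and 50% in failures, the true values are:

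- Control: 0.55·0.20 + 0.45·0.50 = 33.5%.
- Ruxolitinib: 0.75·0.20 + 0.25·0.50 = 27.5%.

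| Assumed mortality, responders / failures | True difference (control minus ruxolitinib) | All failures lost | Only control failures lost |
|---|---|---|---|
| 20% / 40% | 4 points | 0 | −5 |
| 20% / 50% | 6 points | 0 | −7.5 |
| 20% / 60% | 8 points | 0 | −10 |
| 30% / 50% | 4 points | 0 | −5 |

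These are extreme cases under assumed mortality. They show the direction of the risk and do not forecast the trial's result.

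**The case against.** The strongest reply is that one sentence stands against many. The rest of 5.4.2 stops data collection only on withdrawal of consent, Section 4.7 follows everyone for survival, Section 6.5.3 covers patients with progression or new therapy, and Section 7.5.5 follows relapse during treatment and follow-up. A sensible site would read the sentence as meaning withdrawal from treatment. Section 8.4 also provides multiple imputation and best-case/worst-case analyses. This stands as far as it goes: loss of data is a possibility, not a certainty.

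Three stronger readings are tempting, and the documents do not support them.

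- *That the rule selects treatment failures.* Section 6.2 uses permanent discontinuation of study drug to mark the end of any patient's treatment period. Read literally, the sentence would also remove responders who finish their taper.
- *That about 45 and 25 patients would lack Day-28 status.* Those are expected Day-28 non-responders, who are by definition classified on the primary endpoint. Section 7.5.1 also schedules weekly grading for 8 weeks from randomisation. The number who stop early and miss Day 28 is not given.
- *That the study-end rule in Section 4.7 threatens the Month-24 endpoints.* With the 1-year OS of 73.4% in Section 1.3 and an assumed constant hazard, 75% mortality is reached at ln 4 / 0.309 = 4.5 years, or about 2.4 to 28 years across the quoted interval of 56.6% to 95.1%. This counts deaths only, but it falls after Month 24, so harm is not shown.

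The reply does not remove the contradiction, and the friendlier sections leave gaps. The GVHD follow-up in 6.5.2 excludes patients who stopped for GVHD progression. Section 6.5.3 then asks only about new therapy and survival. Section 7.5.2 does not list chronic GVHD assessment during follow-up.

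**Conclusion.** The contradiction is in the text. The first sentence of 5.4.2 conflicts with 4.6, 4.7, 5.4, 5.4.3, 6.5.3 and the rest of its own section, and with intention-to-treat analysis of Month-24 endpoints. A loss of about 22% to 35% of patients, against 10% allowed, is an illustration. It rests on literal application of the sentence, on non-response standing in for stopping study drug, and on the plan's assumed response rates. More losses in the control arm would follow under the same assumptions, but the protocol does not establish such an imbalance. The point is a correctable conflict in the instructions on follow-up, and the sample size is unaffected.

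**What to change.** In 5.4.2, replace withdrawal from the study by withdrawal from study treatment. Reconcile 5.4, 5.4.2, 6.5.2 and 6.5.3, so that Day-28 and Day-56 response, new GVHD therapy, relapse, chronic GVHD and survival are collected to Month 24 regardless of treatment status, unless the patient withdraws consent for data collection.

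Separately, the Synopsis, 5.1.1.1 and 5.4.1 do not agree on whether treatment continues or stops in refractory GVHD. They must be reconciled by those responsible for clinical management, because the answer decides who counts as having stopped study drug.

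The cost is a short amendment and a reminder to sites. Patients who stopped for GVHD progression would supply some additional data, at contacts that 6.5.3 already plans.

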**If a subject is withdrawn from study treatment:**

- The study monitor or sponsor must be notified.
- The reason(s) for withdrawal must be documented in the subject's medical record and in the eCRF.
- The EOT visit should be performed.
- The date of the EOT visit should be registered in the IVRS.
- Subjects must be followed for safety until the time of the follow-up visit or until study drug–related toxicities resolve, return to baseline, or are deemed irreversible, whichever is longest.

If the subject discontinues study treatment and actively withdraws consent for collection of follow-up data (safety follow-up or disease assessment), then no additional data collection should occur; however, subjects will have the option of withdrawing consent for study treatment but continuing in the follow-up period of the study for safety/efficacy assessments.

